## Abstract

**Background:**

Critically ill patients rapidly develop muscle wasting resulting in sarcopenia, long-term disability and higher mortality. Bolus nutrition (30–60 min period), whilst having a similar incidence of aspiration as continuous feeding, seems to provide metabolic benefits through increased muscle protein synthesis due to higher leucine peaks.

To date, clinical evidence on achievement of nutritional goals and influence of bolus nutrition on skeletal muscle metabolism in ICU patients is lacking. The aim of the Pro BoNo study (Protein Bolus Nutrition) is to compare intermittent and continuous enteral feeding with a specific high-protein formula. We hypothesise that target quantity of protein is reached earlier (within 36 h) by an intermittent feeding protocol with a favourable influence on muscle protein synthesis.

**Methods:**

Pro BoNo is a prospective randomised controlled study aiming to compare the impact of intermittent and continuous enteral feeding on preventing muscle wasting in 60 critically ill patients recruited during the first 48 h after ICU admission. The primary outcome measure is the time until the daily protein target (≥ 1.5 g protein/kg bodyweight/24 h) is achieved. Secondary outcome measures include tolerance of enteral feeding and evolution of glucose, urea and IGF-1. Ultrasound and muscle biopsy of the quadriceps will be performed.

**Discussion:**

The Basel Pro BoNo study aims to collect innovative data on the effect of intermittent enteral feeding of critically ill patients on muscle wasting.

**Trial registration:**

ClinicalTrials.gov NCT03587870. Registered on July 16, 2018. Swiss National Clinical Trials Portal SNCTP000003234. Last updated on July 24, 2019.

## Strengths and limitations of this study

The study’s main strength is the implementation of an advanced and promising therapy for an unsolved problem: rapid muscle wasting in critically ill patients. The short intermittent feeding times in the experimental group (a total of 2 h feeding time and total break time of 22 h) may allow more flexible patient care compared to the continuous control group (a total of 20 h feeding time and total break time of 4 h).If the short intermittent feeding times are well tolerated, patients in the experimental group are expected to reach the daily protein target faster, as there are fewer feeding interruptions.Until today, there is no known study that directly measures muscle atrophy by ultrasound and biopsy in relation to differing feeding protocols in critically ill patients. Due to the quantitative measurement of the quadriceps muscle by ultrasound and histological evaluation of biopsies, the study could provide new reliable data in the field of muscle wasting in critically ill patients and a direct comparison of the two feeding regimens.The study is limited by the wide heterogeneity of type and severity of underlying disease of intensive care unit (ICU) patients included in the study. These variable conditions will be addressed according to assessment and analysis of the Simplified Acute Physiology Score II (SAPS II) score.

## Introduction

### Background and rationale

Acute skeletal muscle degradation in intensive care unit (ICU) patients is associated with functional impairment and increased short- and long-term morbidity [1, 2]. Muscle weakness in ICU patients occurs early and rapidly due to stress metabolism, immobility and malnutrition [3, 4]. Physical disability can persist up to 5 years [5], or possibly even longer. The loss of muscle mass seems to be accented during the first 2 to 3 weeks of immobilisation [6]. Moreover, malnutrition represents an important factor contributing to muscle wasting [7]. Therefore, adequate nutritional support could contribute to diminish muscle wasting in ICU patients.

Oral intake of 20 g protein per meal for healthy, respectively 30 g protein for the elderly, is needed for adequate muscle protein synthesis (MPS) [8]. When comparing the two main components of milk protein casein and whey protein, the latter has gained more and more importance in MPS [9]. Whey protein is digested faster and stimulates postprandial amino acid accretion more effectively [9–11]. Regarding MPS, the vital role of the essential amino acid leucine, naturally available in relevant amounts when administering whey protein (1.13 g leucine/100 ml) [12], has been described in prior investigations [10, 13, 14]. In 2015, Marik [1] suggested feeding whey-based nutrition formulas to critically ill patients, and in 2017, Heyland et al. [15] proposed aiming for high-protein nutrition targets (minimum 1.2–1.5 g protein/kg bodyweight (BW)/24 h, maximum 2.0–2.5 g protein/kg BW/24 h) in ICU setting. To the best of our knowledge, to date, no trial investigating the impact of high-protein whey-based formulas on muscle state of critically ill patients has been performed.

The administration of intermittent feeding (IF) versus continuous feeding (CF) is a topic of ongoing controversy [1, 16–24]. The possible benefits of IF have overcome concerns of adverse effects such as pulmonary aspiration and have blazed a trail for further investigations challenging the definition of continuous feeding as the standard for ICU patients [21, 25]. Insulin plays an essential role in MPS in the presence of amino acids and importantly blunts muscle protein breakdown [26]. Earlier investigations reported that MPS could only be stimulated for a limited time in healthy individuals, despite sufficient availability of amino acids [27]. Another study in healthy men revealed that plasma insulin concentrations increased significantly to a maximum of + 303% for 60 min after application of an oral protein bolus and then decreased after 90 min [8]. Moreover, in 2015, Hooper and Marik suggested in their reviews based on the findings of trials in humans and animals that enteral nutrition given continuously would even reduce protein synthesis [1, 11].

In addition, compared to continuous feeding, IF is assumed to have direct potential advantages over gastrointestinal-hormone secretion [21, 28] and indirect advantages due to preservation of pancreatic and gallbladder function [21], elevated insulin secretion [28, 29] and improvement of glucose control [1]. However, whether this physiologic hormone pattern translates into molecular muscle anabolism remains unknown.

In this study, we hypothesise that target quantity of protein is reached earlier (within 36 h) with enteral IF compared to standard CF. In addition, we expect IF to be equally well tolerated, incidence of adverse events to be similar between groups and MPS to be higher in the experimental group.

### Objectives

The Pro BoNo study (Protein Bolus Nutrition) combines administration of a high-protein whey-based enteral formula with IF to investigate the effects on MPS and muscle rebuilding in ICU patients by muscle biopsy [8, 25, 30] and ultrasound [31–33]. CF with the same formula will be performed in the control group. The potential of IF to reach nutritional goals earlier will be assessed. In addition, adverse effects of IF such as gastrointestinal symptoms, metabolic parameters (blood glucose) and aspiration will be analysed.

For information on overall risk of mortality, organ dysfunction, disease severity and nutritional state of studied patients, standardised scores will be utilised.

### Trial design

The Basel Pro BoNo is a prospective randomised controlled unblinded, investigator-initiated, single-centre study in critically ill patients expected to require nutritional support on the ICU for at least 5 days.

## Methods: participants, interventions and outcomes

### Study setting

Patients will be observed for a maximum of 7 days during their stay in an adult 50-bed ICU admitting medical or surgical patients.

### Eligibility criteria

#### Study population

##### Inclusion criteria

Participants fulfilling the following criteria will be eligible for inclusion in the study:
Inclusion within the first 48 h after ICU admissionAdult patients (aged ≥ 18 years)Expected to receive enteral feeding for at least 5 daysExpected ICU stay of at least 5 days

##### Exclusion criteria

Participants meeting the following criteria will be excluded from the study:
Start of enteral nutrition before ICU admission or study inclusionPregnant or breast feeding women (aged ≤ 45 years will be tested for beta-human chorionic gonadotropin in urine or serum)Clinically significant acute or chronic kidney failure with a glomerular filtration rate (GFR) < 20 ml/minBody mass index (BMI) ≤ 18 or ≥ 35 kg/m^2^Intestinal perforation, peritonitis, intestinal fistula, necrosis or other contraindication to enteral nutritionNoradrenaline ≥ 0.5 μg/kg bodyweight/minInherited/chronic skeletal muscle disorder (e.g. motor neuron disease)Paralysis (e.g. hemiplegia, tetraplegia or paraplegia)Immunosuppression (e.g. due to underlying disease or drug regime)Haematologic malignancySevere coagulopathy at time of inclusion

#### Definition/conditions

##### Inclusion criteria

*Inclusion within the first 48 h after ICU admission.* All patients admitted to the ICU fulfilling the inclusion criteria will be screened for eligibility. Since the study aims to assess beneficial effects of early enteral nutrition, patients not screened within 48 h after ICU admission will not be included in the trial.

*Adult patients (aged ≥ 18 years).* We will only include adult patients in our study.

*Expected enteral feeding of at least 5 days and expected ICU stay of at least 5 days.* For surveillance and comparison of the experimental and control groups, enteral nutrition should be administered for a minimum of 5 days. If the patient leaves the ICU between observation days 5 and 7, the muscle biopsy and the ultrasound measurement will be made at the time of discharge.

##### Exclusion criteria

*Start of enteral nutrition before ICU admission or study inclusion*. To provide the same baseline, patients will only be included whenever they did not receive enteral nutrition before study inclusion.

*Pregnant or breast feeding women*. A negative pregnancy test (i.e. beta-hCG in urine or serum) will be necessary prior to study inclusion in women aged < 45 years.

*Clinically significant acute or chronic kidney failure with GFR < 20 ml/min.* Schwartz et al. [34] concluded that although significant restrictions in protein intake may not be necessary for critically ill patients with acute kidney injury, excessive protein provision in these patients could have a negative effect on renal function and lead to azotaemia. For safety reasons, the GFR value is intentionally set low to exclude patients with severely restricted kidney function.

*BMI ≤ 18 or ≥ 35 kg/m*^*2*^. Patients with underweight or obesity will be excluded from the trial because of altered muscle mass, pre-existing endocrine dysfunction or diverging energy or protein requirements.

*Intestinal perforation, peritonitis, intestinal fistula, necrosis or other contraindication to enteral nutrition.* Gastrointestinal conditions will be excluded to prevent adverse effects of enteral feeding and to decrease the number of patients not completing the study protocol.

*Noradrenaline ≥ 0.5 μg/kg BW/min.* Noradrenaline leads to decreased blood circulation in the muscles. Therefore, analysis of muscle biopsies might be biassed and incision healing negatively affected due to local decrease in blood circulation.

*Inherited and chronic skeletal muscle disorder (e.g. motor neuron disease).* Because of altered muscle metabolism and lower total muscle mass, the analysis of muscle biopsies might be biassed if these patients are included in the study.

*Paralysis (e.g. hemiplegia, tetraplegia and paraplegia).* Because of altered muscle metabolism and lower total muscle mass.

*Immunosuppression (e.g. due to underlying disease or drug regime)*. Patients with immunosuppression suffer from increased risk of infection due to muscle biopsy. Additionally, corticosteroids are known for their influence on muscle breakdown.

*Haematologic malignancy.* Haematologic malignancies might negatively affect blood coagulation and lead to increased bleeding after muscle biopsy.

*Severe coagulopathy at time of inclusion.* Because of increased intramuscular bleeding and haematoma after the muscle biopsy.

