### Assignment of interventions: allocation

#### Sequence generation

Trial staff will have access 24/7 to the electronic case report form (eCRF) where patients are screened and randomised to one of the trial arms. Randomisation will be performed using electronic case report form (REDCap) (see the “Data management” section). A randomisation list will be established using computer-generated random numbers. We will use block randomisation, and patients will be stratified for neurotrauma.

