#### Data management

Study data will be collected and managed using REDCap electronic data capture tools hosted at University Hospital Basel [50]. REDCap is a secure, web-based application designed to support data capture for research studies. REDCap provides (1) an intuitive interface for validated data entry, (2) audit trails for tracking data manipulation and export procedures, (3) automated export procedures for seamless data downloads to common statistical packages and (4) procedures for importing data from external sources.

All data, including demographic data, visit dates, randomisation number and serious adverse events (SAEs), related to this study will be kept within the trial master file (TMF) and the REDCap eCRF. A unique patient study code will be assigned to every screened patient consisting of the prefix PBN (Pro BoNo) plus consecutive numbering for every included patient (e.g. PBN-1). This code will be used to identify all study-specific data (e.g. ultrasound images, blood parameters). The trial will be terminated after collecting data from 30 patients in each group. The signed informed consent forms will be kept in the investigator site file (ISF). To minimise bias, we will set range checks for data values within the eCRF. Data will be archived dually on an external hard disk and on our in-house server system with a backup every 24 h. The hard disk and all physical study data will be stored in a designated place on our ICU at the University Hospital Basel for a minimum of 10 years after study termination or in case of premature termination of this study.

SAEs will be documented in the REDCap eCRF and on paper documents.

Only the study team will have access to study-related data. In case of a patient’s ex post denial of study participation, the data collected will not be used for publication in the present trial or in future trials. In such cases, the data will be destroyed.

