### Statistical methods

#### Statistical methods for primary and secondary outcomes

Detailed methodology for summaries and statistical analyses of the data collected in this study will be documented in a statistical analysis plan elaborated with the Clinical Trial Unit of the University Hospital Basel.

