##### Primary and secondary analysis

A 2-way repeated measures ANOVA with post hoc pairwise comparison using a Bonferroni correction will be used to test for differences in protein administration at each time point for the control and experimental groups. The same method will be used to test differences in all secondary outcomes between groups. Additional statistical modelling using generalised linear models will be performed to inspect relationships between baseline patient characteristics, and primary and secondary outcomes.

All analyses on primary and secondary endpoints will be calculated by the study team in close collaboration with the Clinical Trial Unit of the University Hospital Basel.

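### Daily urea is read as amino acid breakdown and compared without a kidney covariate although GFR from 20 ml/min upwards is admitted: the contrast is unbiased but imprecise and not specific

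*Protocol article*

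**What the plan says.** - **Outcome.** The abstract lists "evolution of glucose, urea and IGF-1" among the secondary outcomes. The Secondary outcome measures section has urea measured once a day in mmol/l and takes it to indicate amino acid breakdown.
- **Test.** The Primary and secondary analysis section names a 2-way repeated measures ANOVA for the primary outcome and adds: "The same method will be used to test differences in all secondary outcomes between groups". It names no covariate for that test.
- **Other modelling.** The same section adds: "Additional statistical modelling using generalised linear models will be performed to inspect relationships between baseline patient characteristics, and primary and secondary outcomes". Kidney function is not named there. Detailed methods "will be documented in a statistical analysis plan elaborated with the Clinical Trial Unit", which is not shown.
- **Who enters.** The exclusion criteria remove only patients with a GFR under 20 ml/min. The definitions section gives the reason: "For safety reasons, the GFR value is intentionally set low to exclude patients with severely restricted kidney function". It also says that "excessive protein provision in these patients could have a negative effect on renal function and lead to azotaemia".
- **Allocation and size.** "We will use block randomisation, and patients will be stratified for neurotrauma". "The trial will be terminated after collecting data from 30 patients in each group".
- **Protein by design.** The planned cumulative protein at the end of day 1 is 1.1 g/kg in Table 1 (intermittent) and 0.65 g/kg in Table 2 (continuous). Both tables reach 1.6 g/kg per 24 h by the end of day 2.

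**The concern.** Plasma urea is set by how much is produced and how fast the kidneys clear it. The outcome definition speaks only of production. The eligibility rule lets clearance vary widely, and the stated test does not account for it.

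Two things are at stake. First, variation between patients in kidney function goes into the error term of the arm comparison, and 30 patients per arm is a small number to absorb it. A real difference in urea production could easily be missed. Second, a difference that is found would be reported as more or less amino acid degradation, although clearance and the amount of protein delivered also move urea.

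**Working it through.** The plan states no power or precision figure for urea, so there is none to reproduce. The documents also give no GFR distribution, no SD of urea and no expected urea difference. Everything numerical below therefore rests on assumptions, which are varied.

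**1. Differences between patients.** At steady state, urea = generation / clearance. With clearance proportional to GFR and equal generation, urea at GFR 20 is 100/20 = 5 times urea at GFR 100. This compares two patients, not two arms.

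**2. Precision of the arm contrast.** Model: log urea = log generation - log GFR. Assumptions: SD of log generation 0.3 (variance 0.09), 30 per arm, two-sided 5%, one urea value per patient, GFR known without error.
- SE without GFR = sqrt[(0.09 + var(log GFR)) x 2/30].
- SE with log GFR as covariate is about sqrt(0.09 x 2/30) = 0.077.
- For GFR uniform on 20-120, var(log GFR) is about 0.229. Its share of the variance is 0.229/0.319 = 72%, and the SE is sqrt(0.319 x 2/30) = 0.146.
- For GFR uniform on 60-120, var(log GFR) is about 0.039. Its share is 30%, and the SE is 0.093.

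Simulation with 4,000 runs per setting, with a true difference of zero or of 0.20 on the log scale (exp(0.20) = 1.22):

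| Assumed GFR (ml/min) | GFR share of variance | Rejection under no effect, unadjusted / adjusted | Power at 0.20, unadjusted / adjusted |
|---|---|---|---|
| Uniform 20-120 | 72% | 5.7% / 5.3% | 27% / 72% |
| Lognormal, median 70, clipped to 20-150 | 67% | 5.1% / 4.7% | 31% / 71% |
| Uniform 60-120 | 30% | 4.6% / 4.7% | 56% / 71% |

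The mean estimated difference was about 0 under no effect and about 0.20 under the true effect, with and without adjustment. Adjustment improves precision and removes no systematic bias.

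**3. Chance imbalance.** With 30 per arm, the difference in mean GFR between arms has an SD of sqrt(2/30) = 0.26 GFR SDs. It exceeds 0.5 SD in about 5% of trials.

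**4. Does the repeated-measures design remove the problem?** Only in part. A stable difference in level drops out of the group-by-time term, but on the mmol/l scale the rise in urea also scales with 1/clearance. For illustration, assume generation rises from 514 to 925 mmol/day and urea clearance is 0.6 x GFR:
- GFR 20: (925 - 514)/(0.6 x 20 x 1.44) = 23.8 mmol/l at steady state.
- GFR 100: (925 - 514)/(0.6 x 100 x 1.44) = 4.8 mmol/l.

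A one-compartment simulation gives power for a true 20% difference in generation. It assumes a urea volume of 45 L, a between-patient SD of 25%, 20% error in measured GFR, 5% assay error, 30 per arm and 1,500 runs, with GFR log-uniform on 20-120:

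| Assumed GFR | Change from baseline | Log urea adjusted for baseline urea and screening GFR |
|---|---|---|
| 20-120 | 42% | 64% |
| 40-120 | 54% | 66% |

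These figures treat fed and unfed generation within a patient as independent. With perfect correlation, and GFR 20-120, change from baseline gives 69% and adjustment about 100%. Adjustment gains in either case.

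**5. Specificity.** Planned protein by the end of day 1 is 1.1/0.65 = 1.7 times higher with intermittent feeding. An early urea difference may therefore reflect intake.

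**The case against.** The strongest reply is that the arms are randomised. A reader might infer from the five-fold range between patients that the arm contrast mostly measures kidney clearance. The documents do not support that: baseline GFR creates no expected difference between randomised arms, and the error rate in the table stays near 5% without adjustment. This part of the reply stands in full.

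It also stands that none of the simulations is the planned multi-day ANOVA. A comparison at one time point overstates the loss for any term that sets aside stable levels, so the change-from-baseline figures are the nearer guide to the group-by-time term. If few patients enter with a low GFR, the gain is modest.

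A third reply is that covariates belong to the analysis plan and that generalised linear models on baseline characteristics are already planned. This holds only in part. Those models are described as additional and as inspecting relationships, while the protocol itself names the between-arm test and the meaning given to urea.

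A reader might also infer that renal harm would be passed off as metabolism. The documents do not show this. The azotaemia sentence is conditional, concerns excessive protein in acute kidney injury and justifies an exclusion. The narrow adverse event list is deliberate and tied to the trial's risk category, and SOFA scores organ dysfunction daily. Kidney function after randomisation is not protected by randomisation, but the documents give no size for any effect of feeding on it.

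**Conclusion.** The point holds as one of precision and interpretation for a single secondary outcome, at low severity. The stated comparison of urea is valid as a test of a difference between arms, but it is less precise than it could be. Under the assumed inputs, power for a 0.20 log difference is about 27-56% without a kidney covariate and about 71% with one. For change from baseline, the corresponding gain is from 42-54% to 64-66% for a 20% difference in generation. The size depends on how widely GFR varies among the patients enrolled, which the documents do not say.

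Separately, no analysis of urea alone supports a statement about amino acid degradation, because kidney clearance and protein delivered also determine it.

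**What to change.** - Analyse log urea over the daily measurements with log baseline urea (the last value before the first feed) and log screening GFR as covariates.
- Word any conclusion on amino acid degradation with kidney function and protein intake over the same days shown alongside by arm.
- State that the adjustment does not correct for kidney injury or renal replacement arising after randomisation. An analysis that omits urea values after the start of renal replacement conditions on a post-randomisation event, so keep it as a sensitivity analysis only.

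The cost is one more covariate model for a secondary outcome, with no new patients or samples. GFR is needed to judge eligibility, and Table 3 schedules laboratory parameters from screening. The article does not say that the GFR value or renal replacement is recorded as study data, so the eCRF should be checked for both.
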